**Protocol:**

**Efficacy of ultrasound-guided peripheral nerve block versus forearm Bierse block in patients undergoing carpal tunnel release: A randomized controlled trial.**

1. **Introduction and hypothesis**

Introduction:

In Belgium, several ways of anesthesia are used to perform hand surgery, being general anesthesia, intravenous regional anesthesia as well as locoregional anesthesia. Locoregional anesthesia and intravenous regional anesthesia are often performed since patients can be discharged from the hospital more rapidly.

A forearm intravenous regional anesthesia (IVRA; mini-Bier’s block) is an effective and safe technique to perform hand surgery, especially since the dose of the used anesthetic is reduced compared to a regular upper arm Bier’s block, leading to a reduced risk of local anesthetic toxicity.

An ultrasound-guided distal peripheral nerve block is often used for hand surgery, in which the nervus medianus and the nervus ulnaris can be affected locally. Research showed that this technique is associated with a reduced surgical procedure time when compared to intravenous regional anesthesia (1).

In the Jessa Hospital, a carpal tunnel release is often performed using the forearm intravenous regional anesthesia. However, to date, the analeptic effectivity of the forearm intravenous regional anesthesia has not been compared to the distal peripheral nerve block.

The primary aim of this study is to compare the analgesic effectivity of the forearm intravenous regional anesthesia versus the ultrasound-guided distal peripheral nerve block. Our hypothesis is that the latter technique is superior. A blinded surgeon will determine the analgesic effectivity of these techniques (graded as “complete” or “incomplete”) and divide the effectivity in 4 grades. Grade 1 and grade 2 are considered “complete” blockade, while grade 3 and grade 4 are considered “incomplete” blockade. Grade 1: complete motor and sensory blockade, grade 2: partial motor blockade but no pain or deep pressure sensitivity, grade 3: partial motor blockade with mild pain requiring rescue local or opioid analgesia, grade 4: incomplete motor- and sensory blockade requiring sedation/conversion to general anesthesia).

Secondary study outcomes are patient’s pre-, intra-, and post-operative pain scores at several time points, measured via an 11-point Numeric Rating Scale (NRS) in which number 0 means “no pain at all”, number 5 means “moderate pain” and number 10 means “worst possible pain”.

General patient satisfaction as well as satisfaction of the surgeon regarding the used technique will be measured via a 7-point Likert Scale, in which number 1 means “extremely dissatisfied” and number 7 means “extremely satisfied”.

Furthermore, the time spend in the operating room, the time of surgical procedure and the use of post-operative medication use will be recorded as well.

1. **Researchers**

[name], [name], [name]. [name]

Anesthesiology, Jessa hospital, Hasselt, België

[name]

Orthopedic Surgery, Jessa ziekenhuis, Hasselt, Belgium

1. **Funding**

This study received no funding.

1. **Outcome measures**

Results will be evaluated on day 0 during admission to hospital and on day 1 with a telephone call.

Primary outcome:

The primary outcome of this study is to compare the analgesic effectivity of the forearm intravenous regional anesthesia versus the ultrasound-guided distal peripheral nerve block. A blinded surgeon will determine the analgesic effectivity of these techniques after the patient is fully ready and surgically covered as this is an observed blinded study. The surgeon will grade the anaesthesia as “complete” or “incomplete” and divide the effectivity in 4 grades. Grade 1 and grade 2 are considered “complete” blockade, while grade 3 and grade 4 are considered “incomplete” blockade. Grade 1: complete motor and sensory blockade with a pincet in the medianus and ulnaris area, grade 2: partial motor blockade but no pain or deep pressure sensitivity, grade 3: partial motor blockade with mild pain requiring rescue local or opioid analgesia, grade 4: incomplete motor- and sensory blockade requiring sedation/conversion to general anesthesia).

Secondary outcomes:

- Pre-operative: pain score at start of anesthesia technique (measured via an 11-point Numeric Rating Scale)
- Pre-operative: pain score at surgical incision (start of surgical procedure) (11-point Numeric Rating Scale)
- Intraoperative: pain score (11-point Numeric Rating Scale) at every 10 min during the surgical procedure (both surgical pain and tourniquet pain)
- Time the patient is in operating room (start by entering the operating room until leaving the operating room)
- Time of surgical procedure (start at surgical incision until closing of the surgical wound)
- Post-operative: average pain score at hospital discharge and at day 1 after surgery
- Post-operative: use of pain medication (paracetamol and/or ibuprofen) after surgery and at day 1 after surgery
- General satisfaction of the patient with the anesthesia technique (measured via a 7-point Likert scale with 1 absolutely not satisfied, 4 neutral and 7 extremely satisfied)
- Satisfaction of the surgeon with the surgical conditions (7-point Likert scale)

1. **Study design**

In this monocentric, investigator-initiated, observer-blinded, prospective, randomized controlled trial, 2 groups of patients that will undergo carpal tunnel release surgery will be compared.

Group 1: mini-Biers Block (standard of care in JESSA hospital)

Group 2: distal peripheral ultrasound-guided nerve block

This study will be performed according to the Declaration of Helsinki and will be approved by the Ethical Committee of the Jessa Hospital before the start of the study. A written informed consent will be obtained before participation in the study.

Randomization will be performed using a computer-generated random allocation sequence, created by the study statistician. Allocation numbers will be sealed in opaque envelopes, which will be opened in sequence by an independent anaesthesiologist who is not involved in the assessment of outcomes.

1. **Study population**

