## 6.4 Sample Size Calculation

Sample size was determined for the primary study outcome with the aim to reject the superiority of the distal peripheral nerve block compared to forearm intravenous regional anesthesia. Based on a retrospective analysis of unpublished data from our hospital, we assume that 75% of patients will have a complete block (grade 1 or2) after a forearm IVRA. Based on a previous study, we assume that 95% of patients will have a complete block (grade 1 or2) after a distal peripheral nerve block (4). By using a binary outcome, we determined the sample size for each group to be 47 (α=0.05, power=0.80). To account for a possible 6% drop-out rate, the sample size was increased to 50 patients per group.

1. **Study procedures**

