**Safety**

All possible complications were explained to the participant preoperatieve. Both interventions, the distal peripheral nerve block and the mini biers block are standard techniques used in the Jessa hospital.

1. **Statistical analysis**

Sample size was determined for the primary study outcome with the aim to reject the superiority of the distal peripheral nerve block compared to forearm intravenous regional anesthesia. Based on a retrospective analysis of unpublished data from our hospital, we assume that 75% of patients will have a complete block (grade 1 or2) after a forearm IVRA. Based on a previous study, we assume that 95% of patients will have a complete block (grade 1 or2) after a distal peripheral nerve block (2). By using a binary outcome, we determined the sample size for each group to be 47 (α=0.05, power=0.80). To account for a possible 6% drop-out rate, the sample size was increased to 50 patients per group.

Descriptive statistics will be presented as frequencies and percentages of the total amount of patients for categorical variables, while numerical variables will be presented as mean ± SD. Group comparison will be performed using Chi-square test (or a Fisher’s Exact test when necessary) for frequencies. Depending on normality, a Mann-Witney U test or a Student’s t-test will be used and a Mixed-model analysis will be used to correct for the multiple measurements of the Numerical Rating Scale (NRS) for pain scores. An average difference of 1.3 points or more on the NRS pain score is considered clinical relevant. A p-value <0.05 is considered statistical significant, while p<0.10 is considered a tendency.

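### Intraoperative surgical and tourniquet pain is scored only at 10-minute points, so an operation closed before minute 10 has no such score and the number of scores depends on procedure length

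*Protocol*

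**What the plan says.** In the Protocol, Outcome measures, Secondary outcomes, pain during the operation is defined as "Intraoperative: pain score (11-point Numeric Rating Scale) at every 10 min during the surgical procedure (both surgical pain and tourniquet pain". Four other statements determine what that schedule yields.

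- Procedure time is a secondary outcome in its own right: "Time of surgical procedure (start at surgical incision until closing of the surgical wound".
- The score at the start of surgery is a separate item under a pre-operative label: "Pre-operative: pain score at surgical incision (start of surgical procedure) (11-point Numeric Rating Scale". It is not split by source of pain.
- The next listed pain score comes after the patient has left theatre: "Post-operative: average pain score at hospital discharge and at day 1 after surgery".
- The Introduction says of the nerve block: "Research showed that this technique is associated with a reduced surgical procedure time when compared to intravenous regional anesthesia".

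For the analysis, the Statistical analysis section says that "a Mixed-model analysis will be used to correct for the multiple measurements of the Numerical Rating Scale (NRS) for pain scores". The protocol lists no score at wound closure and no worst-pain score. It gives no expected procedure length for either arm.

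**The concern.** The 10-minute grid is bounded by the length of the operation. A carpal tunnel release closed before minute 10 contributes nothing to the intraoperative outcome, and one closed between minutes 10 and 20 contributes a single scoring round. The intraoperative item is also the only one that names tourniquet pain, so a short case leaves no tourniquet pain score anywhere in the dataset.

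Duration is observed after randomisation. If it differs between the arms, the patients scored at each point are the longer operations of each arm, and these are no longer the randomised groups. The protocol's own background gives some reason to expect such a difference. At stake are the completeness and, conditionally, the comparability of one secondary outcome. This is a matter of data collection, so a later analysis plan cannot supply scores that were never taken.

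**Working it through.** **What the text fixes.** The operation starts at incision (minute 0) and ends at closure. Minute 0 is covered by the separate incision item, so intraoperative scores fall at minutes 10, 20 and so on. The number of scoring rounds for a patient with duration D is the whole-number part of D/10, and it is zero when D is below 10.

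**Arm size.** The protocol states no figure for the number of intraoperative scores, so there is none to reproduce. The 50 per arm used below comes from section 6.4. That calculation reproduces with the unpooled formula, two-sided alpha 0.05 (sidedness is not stated) and power 0.80: (1.960 + 0.842)² × (0.75 × 0.25 + 0.95 × 0.05) / 0.20² = 46.1, rounded up to 47, and 47 / 0.94 = 50. The present point does not depend on it.

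**Assumptions, not in the documents.** Durations are normal with SD 4 min, and the mean is 2 min shorter with the nerve block. The share with at least one score is P(D > 10) = 1 − Φ((10 − mean)/4).

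| Mean, IVRA v block (min) | (10 − mean)/4 | Any 10-min score | Of 50 per arm |
|---|---|---|---|
| 8 v 6 | 0.50 v 1.00 | 31% v 16% | 15 v 8 |
| 10 v 8 | 0.00 v 0.50 | 50% v 31% | 25 v 15 |
| 12 v 10 | −0.50 v 0.00 | 69% v 50% | 35 v 25 |
| 15 v 13 | −1.25 v −0.75 | 89% v 77% | 45 v 39 |
| 20 v 18 | −2.50 v −2.00 | 99% v 98% | 50 v 49 |

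**Other distribution.** A normal curve is rough for short durations. Lognormal durations with a coefficient of variation of 30% give the following numbers scored of 50: 9 v 1 at 8 v 6 min, 22 v 9 at 10 v 8, 34 v 22 at 12 v 10, 45 v 39 at 15 v 13, 49 v 48 at 20 v 18, and 50 v 50 at 30 v 28. The pattern is the same.

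**Equal durations.** If both means are 10 min, the lognormal version gives 22 v 22. The arms do not differ in numbers, but 28 of 50 in each still have no intraoperative score.

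**Second time point.** P(D > 20) under the normal assumption is 11% v 4% at means of 15 v 13 min and 50% v 31% at 20 v 18 min. For longer operations the imbalance moves from having any score to having a second one.

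**The case against.** The strongest reply is that everything quantitative here is assumed. The protocol gives no duration, no spread and no between-arm difference, and the results run from negligible to large. This stands, and it makes the between-arm part conditional.

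The shorter procedure is a cited background statement, not a trial hypothesis. The cited paper's title concerns operating room efficiency, and the protocol does not say whether incision-to-closure time or forearm IVRA was studied. This also stands.

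A difference in who is scored biases the pain comparison only if duration is related to pain within arms. Nothing in the documents shows that link, so the working counts scored patients and does not estimate a bias in NRS points.

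Every patient still has an incision score, which is a pain rating at the start of surgery in the groups as randomised. A reader might infer that intraoperative pain cannot be compared between the randomised groups at all, or that the scored subsets will certainly differ. The documents support neither reading. If nearly all operations exceed 10 min, the minute-10 comparison is nearly complete, and if durations are equal the numbers scored match. Intraoperative pain is also one secondary outcome, not the stated aim of the trial.

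The planned mixed model accommodates unequal numbers of scores per patient, and which time points enter it may properly be left to the analysis plan. But no model can recover surgical or tourniquet pain in an operation that ended before the first scoring point. One could instead start the grid at minute 0, so that every patient has a score. That would only repeat the separately listed incision item and would still leave short operations unscored after incision.

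**Conclusion.** The structural point holds on the text alone: an operation closed before minute 10 has no intraoperative surgical or tourniquet pain score, and the number of scores is governed by a post-randomisation variable that is itself an outcome.

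The imbalance between arms is conditional. It needs operations of roughly 8 to 15 min on average and a real shortening with the nerve block. Under the stated assumptions the gap in having any score is then about 12 to 19 percentage points. It is negligible at about 20 min or more, and absent in numbers if durations are equal. The primary outcome, which is graded before surgery starts, is unaffected, as are the incision score and the sample size. This is a weakness in one secondary outcome that is worth correcting because the correction is cheap.

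**What to change.** Add to the secondary outcomes an NRS for surgical pain and an NRS for tourniquet pain at wound closure, scheduled for every patient whatever the length of the operation. Include this score in the between-group intraoperative comparison. Keep the 10-minute scores and report the number of patients scored per arm at each point. A score for worst pain during surgery may be added as a supplementary item. Its downside is brief recall, and making it the main intraoperative comparison would be a debatable change of outcome.

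One limit should be recorded. A patient who has been sedated or converted to general anaesthesia may be unable to answer at closure. Section 6.4 assumes that "we assume that 75% of patients will have a complete block (grade 1 or2) after a forearm IVRA" and "we assume that 95% of patients will have a complete block (grade 1 or2) after a distal peripheral nerve block", which leaves 25% v 5% incomplete, or at most about 12 v 2 of 50 if every incomplete block were grade 4. The protocol does not split grades 3 and 4. The reason for any missing closure score should therefore be noted by arm.

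The cost is two short questions from the blinded researcher, who already questions patients during surgery (Study procedures, Peri-operative phase), and a change of wording in the protocol and case report form. No treatment or rescue rule changes.

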**Postoperative phase:**

Post-operative pain medication in the hospital includes paracetamol 15mg/kg (max 1gr) 1x/6h and taradyl 0.5mg/kg (max 30mg) 1x/8h, while contramal serves as rescue medication.

Post-operative pain medication at home includes paracetamol 15mg/kg (max 1gr) 1x/6h or ibuprofen 600mg 1x/8h whenever necessary.

On day 1 after surgery, the patient will be contacted via telephone by the researcher who will question the use of post-operative pain medication, as well as NRS pain scores and patient satisfaction.

1. **Randomisatie en blindering**

Participants will be randomly assigned to 1 of 2 study groups of 50 subjects each: ultrasound-guided peripheral nerve block group or forearm IVRA group. Randomization will be performed using a computer-generated random allocation sequence, created by the study statistician. Allocation numbers will be sealed in opaque envelopes, which will be opened in sequence by an independent anaesthesiologist who is not involved in the assessment of outcomes. Outcome-assessors (surgeon and study assistant) will be blinded to treatment allocation (observer-blinded study).

The surgeon and the researcher will be blinded for the used type of anaesthesia. To reduce a possible deblinding, all patients receive a catheter in the dorsal vein of the hand that will undergo surgery and all patients will receive disinfection on the specific locations on the arm where the ultrasound-guided peripheral nerve block would be performed. In that way, both surgeon and researcher are blinded.

Also, the surgeon and the assessor are asked to leave to operation room and only to enter after the patient is fully installed, desinfected and covered.

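### The postoperative analgesic-use outcome does not match the protocol's own postoperative regimen and does not count the rescue drug

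*Protocol*

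**What the plan says.** The list of secondary outcomes under Outcome measures contains one item on analgesic consumption: "Post-operative: use of pain medication (paracetamol and/or ibuprofen) after surgery and at day 1 after surgery". Two drugs are named in the bracket and no others. The same section fixes the assessment times: "Results will be evaluated on day 0 during admission to hospital and on day 1 with a telephone call".

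The regimen is in the Postoperative phase part of Study procedures. For the hospital stay: "Post-operative pain medication in the hospital includes paracetamol 15mg/kg (max 1gr) 1x/6h and taradyl 0.5mg/kg (max 30mg) 1x/8h", followed by "while contramal serves as rescue medication". For the period after discharge: "Post-operative pain medication at home includes paracetamol 15mg/kg (max 1gr) 1x/6h or ibuprofen 600mg 1x/8h whenever necessary".

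Two other sentences mention medication use without naming drugs. The introduction says that "the use of post-operative medication use will be recorded as well". The Postoperative phase section says that on day 1 "the patient will be contacted via telephone by the researcher who will question the use of post-operative pain medication".

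**The concern.** An analgesic-use outcome in a trial of two anaesthetic techniques is meant to show whether patients in one arm needed more pain relief. For that it has to count drugs whose use depends on pain. At home, paracetamol and ibuprofen are taken as needed, so the day-1 part does this. In hospital the counted drugs fit poorly: paracetamol belongs to the regimen listed for everyone, and ibuprofen is not in the hospital regimen. The drug set apart for patients whose pain is not controlled is not counted.

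The trial's hypothesis is analgesic superiority of the nerve block, so rescue use soon after surgery bears on its question. The pain score at discharge does not fully replace it, because rescue already given can lower that score. If the arms differed in rescue use, the analgesic-use outcome as defined would not show it.

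**Working it through.** The protocol gives no rate of analgesic or rescue use, so this point has no figure to reproduce. The check sets the outcome definition beside the regimen, drug by drug.

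| Drug | Postoperative, in hospital | At home | Tied to need by the protocol? | Counted in the outcome? |
|---|---|---|---|---|
| Paracetamol | Listed at a 6-hour interval | Listed, as needed | At home only | Yes |
| Taradyl | Listed at an 8-hour interval | Not listed | No | No |
| Ibuprofen | Not listed | Listed, as needed | At home only | Yes |
| Contramal | Rescue | Not listed | Yes, in hospital | No |

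1. *Home part.* Both listed home drugs are counted and both are taken as needed. Definition and regimen agree.

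2. *Hospital part.* Of the two counted drugs, only paracetamol is in the hospital regimen, and it is listed there at a set interval. The protocol does not call it scheduled. That reading is inferred from the stated intervals, from contramal being set against them as rescue, and from the as-needed qualifier being attached to the home regimen alone.

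3. *What would move the hospital part.* The Peri-operative phase section already gives paracetamol and taradyl during the operation to all patients without contraindications, and the setting is day surgery. Whether another paracetamol dose falls due before discharge then depends largely on length of stay, which the protocol does not state. Contraindications or refusal could also alter use. None of these is a good marker of analgesic need.

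4. *What is left out.* Let p1 and p2 be the proportions of patients given contramal before discharge in the two arms. Neither is given or can be derived. Whatever the value of p1 − p2, its direct contribution to the outcome as defined is 0, because contramal is not among the counted drugs. The lost information ranges from nothing, if rescue is hardly used in either arm, upwards, and no figure in the protocol sets a limit.

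5. *Reach.* The protocol's one computed figure is the sample size for the primary outcome (75% v 95% complete block). It reproduces with unpooled variance: (0.75 × 0.25 + 0.95 × 0.05) × (1.960 + 0.842)² / 0.20² = 46.1, rounded up to 47 per group. Then 47 / (1 − 0.06) = 50. The section agrees: "we determined the sample size for each group to be 47 (α=0.05, power=0.80". Nothing in this calculation uses analgesic consumption, so it is untouched.

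**The case against.** The strongest reply is that the outcome was never meant to cover the hospital stay. The drug pair in the bracket is the home pair, the only collection step spelled out for analgesic use is the day-1 call, and the item does not mention the hospital, whereas the pain-score item just above it refers to discharge. This has weight, and the period covered is ambiguous. But the item names a time after surgery as well as day 1, and the section says that results are evaluated on day 0 during admission. If the home-only reading were right, the listed secondary outcomes would contain no measure of postoperative analgesic use in hospital, and rescue would still not be counted.

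A second reply is that medication use is recorded generally, so contramal would be captured. It may well be. The two general sentences name no drugs, however, and do not widen the one place where the outcome is defined. A reader might infer that a rescue difference is bound to go unreported. The documents do not support that, only that it would not enter this outcome.

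Two other strong readings also go too far:

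- A reader might infer that the hospital comparison must show the same near-complete use in both arms and so cannot differ. The protocol does not say that every patient receives postoperative paracetamol in hospital, and in day surgery a 6-hourly dose may not fall due before discharge. Use could be anywhere from near none to near all, and it could differ between arms for reasons unrelated to pain.
- A reader might take contramal as the only rescue drug in hospital. The Peri-operative phase section names local anaesthetic, alfentanil or sufentanil for a grade 3 block. Contramal is the only rescue drug named for the postoperative phase.

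It is also fair to say that contramal use could be close to zero in both arms, given the block and the common perioperative analgesics, and that pain scores at discharge and day 1 are compared in any case. Both remarks limit the consequence without removing the mismatch.

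**Conclusion.** The point holds as a mismatch between a stated outcome definition and the protocol's own regimen. It is not a complaint about detail left to an analysis plan, because the protocol itself fixes which drugs count. The day-0 part, as written, would mainly reflect the common regimen and length of stay, and postoperative rescue use would not contribute to it. The day-1 home part is sound.

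This rests on two readings: that the time after surgery includes the hospital stay on day 0, and that the hospital drugs listed at intervals are given regularly and not on demand. If hospital paracetamol were in fact given on demand, the first criticism would weaken, but the omission of rescue would remain.

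The size cannot be stated, since no rescue rate is given. One secondary outcome is affected. The primary outcome, its sample size and its analysis are not. The correction is worth making because it is cheap and bears on the trial's analgesic question.

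**What to change.** Reconcile the outcome item with the Postoperative phase section by rewording the item in two separately reported parts:

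- before discharge: any postoperative contramal rescue, yes or no, by arm;
- at home up to the day-1 call: as-needed use of paracetamol, ibuprofen or any other analgesic, by arm.

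The rewording also settles which period each part covers. The proportion test already planned for frequencies (chi-square, or Fisher's exact test when necessary) serves the yes/no item. No drug, dose or rescue rule changes.

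The cost is one more item to extract and report. The protocol does not name the source for in-hospital medication data, so the sponsor should confirm that contramal use is captured under the general recording statement.
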